**Appendix 1c. Pulmonary function tests according to prevalence of Interstitial Lung Disease.**

| Pulmonary function test measures. | N | ILD present | N | ILD absent | Contrast between groups (95%CI) |
|------------------------------------------|----------|--------------------|----------|-------------------|----------------------------------------|
| Body plethysmography:             |          |                    |          |                   |                                        |
| FEV 1 , %*                    |          |                    |          |                   |                                        |
| FEV 1 low**, no. (%)          |          |                    |          |                   |                                        |
| FVC, %*                                  |          |                    |          |                   |                                        |
| FVC low**, no. (%)                       |          |                    |          |                   |                                        |
| FEV 1 /FVC (ratio)            |          |                    |          |                   |                                        |
| FEV 1 /FVC below 70%, no. (%) |          |                    |          |                   |                                        |
| TLC, %*                                  |          |                    |          |                   |                                        |
| TLC low**, no. (%)                       |          |                    |          |                   |                                        |
| Diffusion test:                   |          |                    |          |                   |                                        |
| DLCO, %*                                 |          |                    |          |                   |                                        |
| DLCO low**, no. (%)                      |          |                    |          |                   |                                        |
| KCO, %*                                  |          |                    |          |                   |                                        |
| KCO low**, no. (%)                       |          |                    |          |                   |                                        |
| 6 min walk test:                  |          |                    |          |                   |                                        |
| Distance, %*                             |          |                    |          |                   |                                        |
| Distance low**, no. %                    |          |                    |          |                   |                                        |
| Desaturation, (Saturation delta)         |          |                    |          |                   |                                        |
| Desaturation below 93% #, no. %          |          |                    |          |                   |                                        |

Value will be means and SDs unless otherwise indicated. \* - % of expected; \*\* - low is defined as below 80% of expected; # - If COPD or emphysema 88%; ILD – Interstitial Lung Disease; ILD present – ILD according to multidisciplinary discussion; FEV1 – Forced Expiratory Volume in One Second; FVC – Forced Vital Capacity; TLC – Total Lung Capacity; DLCO - Diffusing capacity of the Lung for Carbon Monoxide; KCO – Carbon Monoxide Transfer Coefficient. Contrasts for continuous measures will be based on the difference between means with 95% CIs, while dichotomous outcomes will be based on risk differences with 95% CIs.

**Appendix 1d. Pulmonary function tests according to prevalence of Shrinking Lung Syndrome.**

| Pulmonary function test measures. | N | SLS present | N | SLS absent | Contrast between groups (95%CI) |
|------------------------------------------|----------|--------------------|----------|-------------------|----------------------------------------|
| Body plethysmography:             |          |                    |          |                   |                                        |
| FEV 1 , %*                    |          |                    |          |                   |                                        |
| FEV 1 low**, no. (%)          |          |                    |          |                   |                                        |
| FVC, %*                                  |          |                    |          |                   |                                        |
| FVC low**, no. (%)                       |          |                    |          |                   |                                        |
| FEV 1 /FVC (ratio)            |          |                    |          |                   |                                        |
| FEV 1 /FVC below 70%, no. (%) |          |                    |          |                   |                                        |
| TLC, %*                                  |          |                    |          |                   |                                        |
| TLC low**, no. (%)                       |          |                    |          |                   |                                        |
| Diffusion test:                   |          |                    |          |                   |                                        |
| DLCO, %*                                 |          |                    |          |                   |                                        |
| DLCO low**, no. (%)                      |          |                    |          |                   |                                        |
| KCO, %*                                  |          |                    |          |                   |                                        |
| KCO low**, no. (%)                       |          |                    |          |                   |                                        |
| 6 min walk test:                  |          |                    |          |                   |                                        |
| Distance, %*                             |          |                    |          |                   |                                        |
| Distance low**, no. %                    |          |                    |          |                   |                                        |
| Desaturation, (Saturation delta)         |          |                    |          |                   |                                        |
| Desaturation below 93% #, no. %          |          |                    |          |                   |                                        |

Value will be means and SDs unless otherwise indicated. \* - % of expected; \*\* - low is defined as below 80% of expected; ; # - If COPD or emphysema 88%; SLS - Shrinking Lung Syndrome; SLS present – Shrinking Lung Syndrome according to multidisciplinary discussion; FEV1 – Forced Expiratory Volume in One Second; FVC – Forced Vital Capacity; TLC – Total Lung Capacity; DLCO - Diffusing capacity of the Lung for Carbon Monoxide; KCO – Carbon Monoxide Transfer Coefficient. Contrasts for continuous measures will be based on the difference between means with 95% CIs, while dichotomous outcomes will be based on risk differences with 95% CIs.

**Appendix 2.** The prevalence of High-Resolution CT findings among Systemic Lupus Erythematosus patients.

| Groups of HRCT findings     | Subgroups of HRCT findings | N | Positive, no. (%) |
|-----------------------------|----------------------------|---|-------------------|
| Airways                     |                            |   |                   |
|                             | Bronchiectasis             |   |                   |
|                             | Bronchial wall thickening  |   |                   |
|                             | Bronchiolitis              |   |                   |
|                             | Air trapping               |   |                   |
|                             | Other                      |   |                   |
| Pleural                     |                            |   |                   |
|                             | Pleural thickening         |   |                   |
|                             | Pleural effusion           |   |                   |
|                             | Pleuroparenchymal fibrosis |   |                   |
|                             | Other                      |   |                   |
| Interstitial lung disease   |                            |   |                   |
|                             | UIP                        |   |                   |
|                             | Indeterminate for UIP      |   |                   |
|                             | NSIP fibrotic              |   |                   |
|                             | NSIP non-fibrotic          |   |                   |
|                             | HP fibrotic                |   |                   |
|                             | HP non-fibrotic            |   |                   |
|                             | LIP                        |   |                   |
|                             | OP fibrotic                |   |                   |
|                             | OP non-fibrotic            |   |                   |
|                             | Other                      |   |                   |
| Elevated diaphragm          |                            |   |                   |
| Suspect of malignancy       |                            |   |                   |
| Emphysema                   |                            |   |                   |
| Nodules                     |                            |   |                   |
| Cysts                       |                            |   |                   |
| Enlarged pulmonary arteries |                            |   |                   |
| Other                       |                            |   |                   |

HRCT – High-Resolution CT scan; UIP – Usual Interstitial Pneumonia; NSIP – Non-Specific Interstitial Pneumonia; HP – Hypersensitivity Pneumonitis; LIP – Lymphoid Interstitial Pneumonia; OP – Organising Pneumonia. Percentage is of the total study population.

**Appendix 3.** Impact of baseline characteristics and patient related outcome measures that are not presented in table 4, according to groups of thoracic diseases investigated by univariate logistic regression analyses.

| Outcome measure
/
Baseline characteristic   | PD
OR
(95%CI) | Airway
OR
(95%CI) | Pleural
OR
(95%CI) | ILD
OR
(95%CI) | SLS
OR
(95%CI) |
|------------------------------------------------------------|------------------------------|----------------------------------|-----------------------------------|-------------------------------|-------------------------------|
| White population no. (%)                                   |                              |                                  |                                   |                               |                               |
| BMI, kg/m                                      |                              |                                  |                                   |                               |                               |
| Treatment:                                          |                              |                                  |                                   |                               |                               |
| Corticosteroid ever, no. (%)                               |                              |                                  |                                   |                               |                               |
| Corticosteroid current, no. (%)                            |                              |                                  |                                   |                               |                               |
| Hydroxychloroquine ever, no. (%)                           |                              |                                  |                                   |                               |                               |
| Hydroxychloroquine current, no. (%)                        |                              |                                  |                                   |                               |                               |
| Other csDMARDs ever, no. (%)                               |                              |                                  |                                   |                               |                               |
| Other csDMARDs current, no. (%)                            |                              |                                  |                                   |                               |                               |
| BioDMARDs ever, no. (%)                                    |                              |                                  |                                   |                               |                               |
| BioDMARDs current, no. (%)                                 |                              |                                  |                                   |                               |                               |
| Classification criteria EULAR/ACR
criteria, score 0-51, |                              |                                  |                                   |                               |                               |
| Constitutional*, score 0-2                                 |                              |                                  |                                   |                               |                               |
| Haematological*, score 0-4                                 |                              |                                  |                                   |                               |                               |
| Neuropsychiatric*, score 0-5                               |                              |                                  |                                   |                               |                               |
| Mucocutaneous*, score 0-6                                  |                              |                                  |                                   |                               |                               |
| Serosal*, score 0-6                                        |                              |                                  |                                   |                               |                               |
| Musculoskeletal*, score 0-6                                |                              |                                  |                                   |                               |                               |
| Renal*, score 0-4                                          |                              |                                  |                                   |                               |                               |
| SLE disease specific score:                         |                              |                                  |                                   |                               |                               |
| SLEDAI 2K, score 0-105                                     |                              |                                  |                                   |                               |                               |
| PGA, score 0-3                                             |                              |                                  |                                   |                               |                               |
| LLDAS achieved no. (%)                                     |                              |                                  |                                   |                               |                               |
| DORIS remission achieved no. (%)                           |                              |                                  |                                   |                               |                               |
| SLICC DI, score 0-48                                       |                              |                                  |                                   |                               |                               |
| PROMs:                                              |                              |                                  |                                   |                               |                               |
| LIT, score 0-100                                           |                              |                                  |                                   |                               |                               |
| SLAQ, score 0-100                                          |                              |                                  |                                   |                               |                               |
| MRC, score 1-5                                             |                              |                                  |                                   |                               |                               |
| Body plethysmography:                               |                              |                                  |                                   |                               |                               |
| FEV 1 , % ^                          |                              |                                  |                                   |                               |                               |
| FEV 1 low ~ , no. (%)                |                              |                                  |                                   |                               |                               |
| FVC, % ^                                        |                              |                                  |                                   |                               |                               |
| FVC low ~ , no. (%)                             |                              |                                  |                                   |                               |                               |
| FEV 1 /FVC (ratio)                              |                              |                                  |                                   |                               |                               |
| FEV 1 /FVC below 70%, no. (%)                   |                              |                                  |                                   |                               |                               |
| TLC, % ^                                        |                              |                                  |                                   |                               |                               |
| TLC low ~ , no. (%)                             |                              |                                  |                                   |                               |                               |
| Diffusion test:                                     |                              |                                  |                                   |                               |                               |
| DLCO, % ^                                       |                              |                                  |                                   |                               |                               |
| DLCO low ~ , no. (%)                            |                              |                                  |                                   |                               |                               |
| KCO, % ^                                        |                              |                                  |                                   |                               |                               |

|                                   |  |  |  |  |  |
|-----------------------------------|--|--|--|--|--|
| KCO low ~ , no. (%)    |  |  |  |  |  |
| 6 min walk test:           |  |  |  |  |  |
| Distance, % ^          |  |  |  |  |  |
| Distance low ~ , no. % |  |  |  |  |  |
| Desaturation (Saturation delta)   |  |  |  |  |  |
| Desaturation below 93% #, no. (%) |  |  |  |  |  |

Table of planned univariate analysis. \*According to EULAR/ACR 2019 criteria (15). ~ - low is defined as below 80% of expected; ^ - % of expected; # - If COPD or emphysema 88%. PD – Pulmonary according to multidisciplinary discussion; OR - Odds ratio; 95% CI – 95% Confidence Interval; Airway – Airway Disease according to multidisciplinary discussion; Pleural – Pleural Disease according to multidisciplinary discussion; ILD – Interstitial Lung Disease positive according to multidisciplinary discussion; SLS – Shrinking Lung Syndrome according to multidisciplinary discussion; BMI – Body Mass Index; csDMARD – Conventional Disease-Modifying Antirheumatic Drugs; bioDMARDs – Biologic Disease-Modifying Antirheumatic Drugs; SLEDAI 2K – Systemic Lupus Erythematosus Disease Activity Index 2000 (16); PGA – Physician Global Assessment (17); LLDAS – Lupus Low Disease Activity State (18); DORIS – Definition of Remission in SLE (19); SLICC DI – Systemic Lupus International Collaborating Clinics /American College of Rheumatology Damage Index for Systemic Lupus Erythematosus; PROMs – Patient Reported Outcome Measures; LIT – questionnaire inspired by "Lupus Impact Tracker" (21); SLAQ – Systemic Lupus Activity Questionnaire (22); MRC – Medical Research Council Dyspnoea Scale; FEV1 – Forced Expiratory Volume in One Second; FVC – Forced Vital Capacity; TLC – Total Lung Capacity; DLCO - Diffusing capacity of the Lung for Carbon Monoxide; KCO – Carbon Monoxide Transfer Coefficient.

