## **Statistical analyses**

### **Analysis populations**

The primary analyses will be based on the Intention to Survey (ITS) population (14). This principle assesses the effect of all participants investigated for PD stratified by the presence of PD and subtypes of PD. Accordingly, participants allocated to a PD group will be assessed and analysed as members of that group, irrespective of the availability of the various collected characteristics and outcome variables.

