## **Logistical regression: Searching for risk factors that are associated with presence of different forms of PD**

Mock-up Table 4. We aim to explore whether one or more clinical measures collected at baseline are associated with the presence of PD. The dependent variable will be the presence or absence of a PD condition of interest (i.e.,  $Y=1$  if yes, otherwise  $Y=0$ ). Logistic regression is the best approach for identifying predictors when the outcome variable is binary (i.e., presence vs. absence of PD) and the goal is to estimate the association between predictor variables and the probability of the outcome while enabling adjustments for potential confounders. Independent variables, as listed in Table 4 and appendix 3, will be analysed in univariate logistic regression to identify potential associations with clinically significant PD conditions. Odds ratios (ORs) with 95% CIs will be used to quantify the strength of associations, with 95% CIs excluding 1 considered indicative of potential significance. In multiple logistic regression analyses we plan to investigate associations that were significant by univariate analyses, however, only a subset of independent variables will be expected to remain statistically significant and independently associated with PD conditions.

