## **Missing data**

We expect missing data to be Missing Completely At Random. We plan to investigate the possible impact of missing data in sensitivity analyses. Multiple Imputation (MI) is a statistical technique used to handle missing data by creating multiple plausible datasets, analysing each separately, and then pooling the results to account for uncertainty. This approach is particularly useful for sensitivity analyses in cross-sectional descriptive studies, ensuring that findings are robust to different assumptions about missing data. We will also explore the impact of the missing data by applying a best- and worst-case scenario.

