|              | Pleuroparenchymal fibrosis      |                     |
|              | Other                           |                     |
| ILD          |                                 |                     |
|              | UIP                             |                     |
|              | Probable UIP                    |                     |
|              | Indeterminate for UIP           |                     |
|              | NSIP, fibrotic                  |                     |
|              | NSIP, non-fibrotic              |                     |
|              | HP fibrotic                     |                     |
|              | HP non-fibrotic                 |                     |
|              | Pneumonitis                     |                     |
|              | Diffuse alveolar haemorrhage    |                     |
|              | LIP                             |                     |
|              | OP                              |                     |
|              | Other                           |                     |
| SLS          |                                 |                     |
| Vascular     |                                 |                     |
|              | Pulmonary embolism              |                     |
|              | Pulmonary arterial hypertension |                     |
|              | Pulmonary vasculitis            |                     |
|              | Other                           |                     |
| Other        |                                 |                     |
|              | Atelectasis                     |                     |
|              | Infections                      |                     |
|              | Thoracic malignancy             |                     |
|              | Other                           |                     |

PD – Pulmonary Disease; COPD – Chronic Obstructive Pulmonary Disease; UIP – Usual Interstitial Pneumonia; NSIP – Non-Specific Interstitial Pneumonia; HP – Hypersensitivity Pneumonitis; LIP – Lymphoid Interstitial Pneumonia; OP – Organising Pneumonia; SLS – Shrinking Lung Syndrome. The percentage is of the total study population.

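### Appendix 2 gives each HRCT finding its own N but takes percentages of the whole study population, so anyone without an evaluable scan would count as negative

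*SAP*

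**What the plan says.** Appendix 2 tabulates HRCT findings under the column heads "Subgroups of HRCT findings | N | Positive, no" and a percentage. Its footnote fixes the denominator: "Percentage is of the total study population".

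Table 3, which reports diagnoses made at the multidisciplinary discussion (MDD), has no N column. Its footnote reads "The percentage is of the total study population".

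Under Analysis populations, the SAP describes its Intention to Survey principle: "This principle assesses the effect of all participants investigated for PD stratified by the presence of PD and subtypes of PD". Participants stay in their disease group "irrespective of the availability of the various collected characteristics and outcome variables".

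The logistic regression section states: "The dependent variable will be the presence or absence of a PD condition of interest". It codes Y as 1 for yes and 0 in all other cases.

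Under Missing data: "We expect missing data to be Missing Completely At Random". Multiple imputation is planned as a sensitivity analysis, and in addition: "We will also explore the impact of the missing data by applying a best- and worst-case scenario".

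No section says how to classify a participant with no HRCT, an unreadable HRCT or an undetermined MDD status.

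**The concern.** A row-specific N has a purpose only if the number assessed can differ from the total. Appendices 1a to 1d use N columns in just this way, beside pulmonary function tests whose availability varies. The natural reading in Appendix 2 is therefore the number of participants in whom the finding could be judged. The footnote then sets that number aside and divides by everyone, so that a scan that was never obtained or could not be read has the same effect as a negative scan.

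At stake are the HRCT prevalences in Appendix 2, which readers may compare with other imaging series. A related gap concerns diagnoses. Taken literally, the Y coding would place an undetermined diagnosis in the disease-absent group. The SAP handles a similar problem differently elsewhere: under Methods, walk-test saturation readings of inadequate quality become missing values. There is no equivalent rule for HRCT or MDD status.

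**Working it through.** The SAP gives no sample size, no count of missing scans and no expected HRCT prevalence, so there is no planned figure to reproduce. The check is direct arithmetic.

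**Inputs**
- p: true prevalence of an HRCT finding. Assumed 20% for illustration; also 11% and 37%, the ends of the ILD range that the Introduction cites from tertiary-centre studies.
- m: share of the study population without an evaluable HRCT. Not in the SAP; assumed 0%, 5%, 10% and 20%.
- Mechanism: missing completely at random, the SAP's own expectation.

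**Step 1: the two denominators.** Let T be the total and N = T(1 − m) the number assessed. Expected positives are p × N.
- Divided by N: p.
- Divided by T, as the footnote says: p(1 − m).

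The relative understatement is m.

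**Step 2: numbers.**

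| True p | m = 0 | m = 5% | m = 10% | m = 20% |
|---|---|---|---|---|
| 11% | 11.0% | 10.45% | 9.9% | 8.8% |
| 20% | 20.0% | 19.0% | 18.0% | 16.0% |
| 37% | 37.0% | 35.15% | 33.3% | 29.6% |

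**Step 3: relation to the planned sensitivity analysis.** The SAP does not define its two scenarios. If they mean all unassessed negative and all unassessed positive, then p = 20% and m = 10% give 18% and 18% + 10% = 28%. The footnote's percentage is the lower of these two extremes, presented as the main figure.

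**Step 4: regression coding.** Suppose 10% of outcomes are undetermined at random and coded 0, with assumed prevalences of 20% and 10% in two groups.
- True odds ratio: (0.20/0.80) / (0.10/0.90) = 2.25.
- After coding: (0.18/0.82) / (0.09/0.91) = 2.22.

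The shift is towards 1, but small.

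**The case against.** The strongest reply is that nobody may be unassessed. Methods describes the full set of tests as done on one visit day, followed by diagnosis at the MDD, and the analysis population is those investigated for pulmonary disease. If every scan was evaluable, N equals the total in every row and the footnote does no harm. Appendix 2 is also descriptive, and a reader given both N and the count could recompute the percentage. All of this stands as a limit on size. It does not reconcile the column with the footnote.

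Three stronger readings are tempting, and the SAP does not support them.

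- *The primary prevalence is understated.* Table 3 has no N column, and it reports MDD diagnoses, so its total may equal the number classified. Pulmonary disease here includes asthma, COPD, pleuritis and pulmonary embolism, and the MDD also has the history, lung function and laboratory results. A missing HRCT therefore does not mean that pulmonary disease was not assessed.
- *The Y coding sets a wrong prevalence denominator.* It is ordinary binary coding in the regression section and governs odds ratios only. What it lacks is a statement on undetermined status.
- *The missing-data analyses cannot help.* The SAP does not exclude disease status from them. They can bound the effect once undetermined status is recorded as missing.

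It would also be wrong to limit Table 3 to participants with a scan plus those diagnosed without one. Take 100 patients, 50 with disease, and 10 unscanned of whom 5 are cases and 4 of these are known by other means. Known cases are 45 + 4 = 49. That rule gives 49/(90 + 4) = 52.1%, against a true 50% and 49% on the total. If the other six were recorded as undetermined, the bounds would be 49/100 = 49% and 55/100 = 55%, which contain the true value.

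**Conclusion.** The point holds for Appendix 2. Its N column and its footnote contradict each other, and wherever N is below the total the stated rule understates the prevalence of an HRCT finding by the relative amount m. That is 1, 2 or 4 percentage points on a true 20% for assumed m of 5%, 10% or 20%, and nothing at m = 0. The figures rest on scans being missing completely at random. The SAP does not give m, so neither the existence nor the size of a bias in the results can be shown from it.

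For Table 3 and the regressions the defect is narrower: there is no rule for an undetermined MDD status. A bias in the primary prevalence is not demonstrated.

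**What to change.** 1. In Appendix 2, divide each count by the row N, defined as participants with an evaluable HRCT for that finding, and change the footnote to say so. The cost is one footnote and slightly smaller denominators. The Deviations section renumbers this table as Appendix 3 and adds two ILD categories but records no change of denominator, so the same correction applies to the reported table.
2. For Table 3 and the regressions, keep the MDD classification as planned. Add one sentence: where the MDD left the status of a condition undetermined, it is missing and not Y=0. Report the number undetermined.
3. Under Missing data, state that the best- and worst-case analysis covers undetermined MDD status, and define the two cases as all undetermined negative and all positive.

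If every participant was scanned and classified, no number changes.
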